#### Caregivers

Informal caregivers (spouse/partner, parents, children, siblings) of enrolled DoC patients are recruited for the caregiver study part. For each patient, only one relevant caregiver can be included in the study. Caregivers have to give informed written consent in order to participate, and must be between 18 to 85 years old. Exclusion criteria include: not knowledgeable about local language, severe current psychiatric comorbidity, and cognitive problems/neurodegenerative disease (inability to fill out questionnaires). Caregivers are free to drop out of the study any time they wish so; they anyway drop out from protocol in case of decease of their enrolled DoC patients.

### Measures and data analyses

#### qEEG

Quantitative EEG (qEEG) is recorded using locally available EEG systems (either 21 electrodes standard clinical systems or higher density systems with ≥ 32 electrodes, c.f. Table 3). For each patient, resting-state data as well as task-based data are collected at time points T1 and T2.

**Table 3 Tab3:** Higher-density EEG recording systems used at the different study sites

Study site	System	Number of channels
Germany - Burgau	EGI400	256 electrodes
Germany - Munich	BrainVision	62 electrodes + 2 EOG channels
Israel	Biosemi	64 electrodes
Italy	BrainVision	60 electrodes + 2 EOG channels + 2 EKG channels
France	EGI300	256 electrodes

Resting-state recordings are run for at least 10 minutes continuously. Task-based conditions comprise two paradigms: a motor command protocol [31] and a local-global protocol (a two-level hierarchical oddball auditory protocol) [32]. For both protocols, stimuli are generated via a custom-built stimulation box (provided by the French project partner) which is connected to the specific recording EEG system of each site. Auditory stimuli (local-global paradigm) and pre-recorded standardized task instructions (motor command protocol) are presented to the patient via either headphones or loudspeakers at 70dB.

The motor command protocol consists of six block of eight trials alternating between the instructions “keep opening and closing your right/left hand” and “stop opening and closing your right/left hand”. The 10 seconds of EEG recording after the instructions were given are extracted and segmented in five epochs, each 2 seconds long. This procedure results in 480 epochs (5 epochs × 2 instructions × 8 trials × 6 blocks).

The local-global paradigm evaluates the processing of auditory irregularities [32]. For each trial 5 consecutive brief sounds (50 milliseconds duration) are presented with a 150-millisecond break between the sounds’ onsets and an inter-trial interval of 1350 - 1650 milliseconds. The fifth presented sound is either identical or different to the preceding four sounds, in that way defining the local level of auditory regularity. In addition, regularity can vary on a global level across trials (~80% frequent trials following regularity vs. ~20% violating regularity). In this way, two possible block conditions arise: BLOCK XX: with stimuli, local standard-global standard (frequent stimulus = 5 identical sounds), local deviant-global deviant (infrequent stimulus = 4 identical sounds followed by a 5th different sound), and BLOCK XY: with stimuli, local deviant-global standard (frequent stimulus = 4 identical sounds followed by a 5th different sound), and local standard-global deviant (infrequent stimulus = 5 identical sounds). During the patient assessments, every block condition consisting of 154 trials each is performed twice in a randomized order (1232 trials in total). Before the beginning of each block, patients are instructed to pay attention to the sounds.

EEG markers are extracted using the Python programming language. Pre-processing and computation of state-of-consciousness markers [26, 33, 34] use a designated software library (https://github.com/nice-tools/nice) built on top of the open source software libraries MNE [35]. Other indices quantifying simple and clinically relevant EEG features, such the EEG slowing, will be computed. Specifically, the spectral slope, which has been shown to accurately discriminate conscious from unconscious states in awake and anesthetized healthy subjects, will be estimated through a Matlab-based code that is freely available online [36].

#### TMS-EEG

TMS-evoked potentials (TEPs) are recorded using a TMS-compatible 64-channel Brainamp EEG amplifier (Brain Products GmbH, Germany) integrated with an MRI-guided neuronavigation system that ensures target reproducibility over subsequent sessions. Up to six cortical TMS targets are stimulated (one left and one right medial frontal sites, one left and one right medial parietal sites, one left and one right medial occipital sites) at different intensities spanning from 120 to 200 V/m [37–40]. During TMS-EEG recording, a customized noise [41] is played through in-ear earphones to mask the TMS click. Both single-trial and average TEPs are visually monitored in real time using the software rt-TEP [42] control for the possible contribution of artifacts and to maximize the impact of TMS on cortical neurons.

Following rejection of trials containing noise or muscle artifacts, EEG data are average referenced, high-pass filtered (1 Hz) and baseline corrected over 400 ms pre-stimulus. Independent Component Analysis (ICA) is applied to reduce ocular and residual muscle artifacts. Finally, data are low-pass filtered at 45 Hz. For each cortical target, a TMS-evoked response is obtained by averaging 150-250 artifact-free single trials. In order to obtain the overall amount of electrical activity induced by TMS, the Global Mean Field Power (GMFP) is computed from the multichannel average. Source modeling of TMS evoked potentials is performed only at the latencies corresponding to significant GMFP activations. To assess the threshold for significance, a bootstrap method (which does not assume normality) is applied by shuffling the time samples of pre-stimulus activity (from -300 to -50 ms) at the single-trial level and by calculating 500 surrogated pre-stimulus GMFPs. From each random realization, the maximum value across all latencies is selected to obtain a maximum distribution (control for type I error) and significance level is set at p<0.01. A similar procedure is applied to TMS-evoked responses recorded at single EEG channels. To evaluate the occurrence of pathological OFF-periods that may disrupt the emergence of global complex cortico-cortical interactions, time-frequency decomposition of TEPs is computed as described in [40]. Following theoretical considerations that link consciousness to the observation of complex EEG activity patterns that are integrated and differentiated at the same time, the Perturbational Complexity Index (PCI) [37, 43] is computed for each stimulation site and the individual maximum PCI value is used for diagnostic purposes. The prognostic contribution of all these neurophysiological measures is evaluated by comparing their longitudinal modulation with the clinical evolution of the patient. Notably, the tools and procedures described above will be shared by the Italian unit, which in the last two decades significantly contributed to the TMS-EEG field, with the German unit, the only other one provided with the proper equipment to carry out TMS-EEG measurements.

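### The TMS-EEG significance threshold is built from samples inside the baseline-correction window, so its stated p<0.01 control fails when the EEG is dominated by activity below about 2 Hz

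*Protocol article*

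**What the plan says.** The protocol article, TMS-EEG section, fixes the order of processing. After trial rejection, "EEG data are average referenced, high-pass filtered (1 Hz) and baseline corrected over 400 ms pre-stimulus". Independent component analysis follows, and then: "Finally, data are low-pass filtered at 45 Hz". Each response is an average of 150 to 250 clean trials.

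The null distribution comes from "shuffling the time samples of pre-stimulus activity (from -300 to -50 ms) at the single-trial level" and from "calculating 500 surrogated pre-stimulus GMFPs". From each surrogate, "the maximum value across all latencies is selected to obtain a maximum distribution (control for type I error) and significance level is set at p<0.01".

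The result has two stated uses. Source modelling is confined to latencies at which the GMFP exceeds the threshold. In addition, "A similar procedure is applied to TMS-evoked responses recorded at single EEG channels".

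The qEEG section shows that slow activity matters in this population: "Other indices quantifying simple and clinically relevant EEG features, such the EEG slowing, will be computed". No EEG spectrum is given for the patients.

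**The concern.** The null to be tested is that TMS evokes nothing, so that the post-stimulus GMFP is only averaged background EEG. A pre-stimulus segment can stand in for that only if it has the same variance as post-stimulus background after the same processing.

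Here it need not. The segment from -300 to -50 ms helped to form the mean that was subtracted from it, so part of its slow activity has gone. The post-stimulus samples had a mean subtracted to which they did not contribute, so slow activity drifts away from it and adds variance. Averaging over trials scales both sides equally and does not remove the mismatch.

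At stake are the latencies that enter source modelling and the channel-level results. The section evaluates its measures by setting their change over time against clinical evolution. A change in activity below 2 Hz between visits could therefore shift the significant latencies without any change in the evoked response.

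**Working it through.** **Inputs from the article (TMS-EEG section).** 1 Hz high-pass; 400 ms pre-stimulus mean removed; 45 Hz low-pass; shuffle window -300 to -50 ms; 500 surrogates; maximum over latencies; level 0.01; 150-250 trials; 64-channel amplifier.

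**Assumed, because the article does not give them.** The EEG spectrum, the number of independent spatial sources (8, varied from 1 to 15), the sampling rate (250 or 500 Hz) and a tested window of 0-300 ms.

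**Step 1: which frequencies are affected.** Take a sinusoid of frequency f (Hz) and random phase, and write sinc(x) = sin(πx)/(πx). The baseline mean has relative amplitude s = sinc(0.4f) and is centred at -200 ms. The shuffle window is 250 ms long and centred 25 ms from that point. The tested window is 300 ms long and centred 350 ms from it. The power after subtraction, relative to the power before, is

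- null window: 1 + s² - 2s·sinc(0.25f)·cos(2πf·0.025)
- tested window: 1 + s² - 2s·sinc(0.3f)·cos(2πf·0.35)

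At 1 Hz, s = 0.757. Null window: 1 + 0.573 - 2(0.757)(0.900)(0.988) = 0.23. Tested window: 1 + 0.573 + 2(0.757)(0.858)(0.588) = 2.34.

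| f (Hz) | null window | tested window | ratio |
|---|---|---|---|
| 1 | 0.23 | 2.34 | 10.3 |
| 1.5 | 0.49 | 1.95 | 4.0 |
| 2 | 0.77 | 1.13 | 1.5 |
| 2.5 | 1.00 | 1.00 | 1.0 |
| 3 | 1.11 | 1.06 | 0.95 |
| 4 | 1.04 | 1.08 | 1.05 |

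The mismatch is large up to about 1.5 Hz, modest at 2 Hz and absent from 2.5 Hz.

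**Step 2: error rate with no evoked response.** The documented pipeline was simulated with Gaussian noise (about 60 channels, 200 trials), and the simulation was repeated with separate code. Main runs had 80 to 150 replicates, with standard errors of about 1 to 5 percentage points; some comparison runs had 60. Most runs used 200 or 300 surrogates for speed. The figure is the share of null averages with at least one GMFP sample above threshold.

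| Spectrum | with 400 ms subtraction | without it |
|---|---|---|
| alpha peak + 1/f | 0% | - |
| 1/f | 2.5-8% | - |
| 1/f^2 | 20-30% | 0-3% |
| 1/f^3 | 47-58% | 1-3% |
| 1.5 Hz peak | 42.5-60% | 0-2.5% |
| 2 Hz peak | 5-12.5% | - |
| 2.5-3 Hz peak | 0-1.25% | - |
| 5 Hz peak | 0% | - |

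The stated 1% is thus met, within simulation error, for alpha-dominated EEG and for peaks at 2.5 Hz or faster. Post/pre variance ratios were about 1.2 (1/f), 1.9 (1/f^2) and 3.0 (1/f^3), and 1.00 without the subtraction. Dropping that one step removes most of the excess, so it is the cause.

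**Step 3: sensitivity.** With 4 to 15 sources the rate was 13-42% for 1/f^2 and 28-78% for 1/f^3; with 150 trials and 1/f^3 it was 63%. For single channels it was 9-15% across 1/f^2 to 1/f^3. Pilot runs of only 40 replicates gave 10% for 1/f^2 with the subtraction and 7.5% (3 of 40) for 1/f^3 without it. The longer runs gave 20-30% and 1-3%.

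**The case against.** Most of the case on the other side stands, and it narrows the point.

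- **Not all slow EEG.** A reader might infer that any patient with EEG slowing gets false responses. Steps 1 and 2 do not support that: slowing to 2.5-5 Hz leaves the test near nominal.
- **Shuffling is not the fault.** Destroying autocorrelation may look like a second defect. By itself it raises the threshold of the maximum statistic, which is conservative.
- **Not the diagnosis.** A reader might infer that the PCI, or a responder label, is compromised. The article uses the individual maximum PCI for diagnosis without linking it to this threshold, obtains the OFF-period measure by a cited time-frequency method, and classifies no patient as responder or non-responder by this test.
- **No-response case only.** The article describes real-time monitoring to maximise the cortical effect, so a complete absence of response may not be typical. The number of false latencies beside a genuine response was not examined.
- **Condensed description.** Filter order, and any second baseline step after independent component analysis, are not shown. Varying the high-pass order from 1 to 4 still gave 21-30% for 1/f^2 with 150 trials.

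What remains is that the article itself fixes both windows, the maximum statistic and the level, and claims type I control. For EEG dominated by very low frequencies that claim fails.

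**Conclusion.** The point holds as a calibration fault with a defined range. The direction follows from the stated windows alone. The size rests on assumed spectra and spatial structure: roughly 20-60% instead of 1% for steep (1/f^2 to 1/f^3) or 1.5 Hz spectra, wider still if the number of sources varies; about 3-8% for 1/f; near nominal from 2.5 Hz upwards. How many enrolled patients fall in the affected range cannot be told from the article. The demonstrated consequence is limited to the choice of latencies for source modelling and to the channel-level test. It should be corrected, because the stated error control is wrong for some of the patients this study may enrol and the remedy is cheap.

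**What to change.** For the significance test only, compute both the shuffled surrogates and the tested post-stimulus GMFP and channel responses on the 1 Hz high-passed data, without the 400 ms subtraction. Keep the shuffle window, the 500 surrogates, the maximum statistic and the 0.01 level. Baseline-corrected data can still be used for display and source amplitudes.

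The cost is a small change of analysis code and one revised sentence in the TMS-EEG section. No new data or procedures are needed, and recordings already made can be re-analysed. The threshold rises somewhat in patients with very slow EEG, so some weak late responses will no longer be significant. For the steepest spectrum the error may stay slightly above 1%.

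Randomly sign-flipping whole post-stimulus trials is a tempting alternative and was well calibrated with no response (0-3.3%). It should not be the main fix. The evoked response stays in the surrogates: an early peak equal to the single-trial baseline RMS raised the threshold by 24-33%, and one twice that size slightly more than doubled it. In another run the threshold rose about 1.5-fold with a moderate early peak and 2.7-fold with a large one. A strong early response could thus hide weaker late ones.

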#### (f)MRI

For time points T1 and T2, patients undergo the following 3T MRI protocol with a 64-channel head/neck coil:T2-weighted and FLAIR-3D scans for lesion characterization and masking.High resolution 3D-T1-weighted images for the evaluation of the brain morphometric pattern.Diffusion-weighted images to evaluate the microstructure of the white matter, the main beams and the structural connectivity. Reverse phase encoding in a subsequent otherwise identical second run is applied to minimize susceptibility-induced distortions during post-processing.Susceptibility weighted imaging as an iron sensitive MR sequence to detect potential abnormalities like iron deposition in the brain, hemorrhages, micro bleeds and calcification.Resting-state fMRI sessions as well as their preceding field maps (phase and magnitude images) for functional connectivity analyses.

Prior to the preprocessing step, if possible, lesion maps are drawn using a semi-automatic software MRIcron (https://www.nitrc.org/projects/mricron/). The T1-weighted and functional scans are preprocessed using the fMRIprep package [44] (https://fmriprep.org/en/stable/index.html), which strives for robustness of preprocessing across different sites and scanners. fMRIPrep performs minimal preprocessing including motion correction, field unwarping, normalization, bias field correction, brain extraction, etc. Spatial smoothing is performed additionally, nuisance regression as well as normalization of the structural and functional data into a clinical template (mean age 65 years) [45]. The first five volumes of the functional scan are removed in order to ensure signal stability. Structural images are quantified using regional brain volumetry [46], functional images by quantifying functional networks [47], and dynamical interactions between brain areas [48].

#### Nasal airflow and respiration

A wearable recording device called the “Nasal Holter”, that was developed by the Israeli project partner, is used for assessment of nasal airflow and respiration. The body of the device contains batteries, a processor, two precise pressure sensors, on-board memory, and bluetooth, all encased in silicone. The device is ~7cm long, ~1.5cm wide, ~0.8cm thick, and weighs only ~10 grams. The holter is secured by a skin-safe sticker to the patient‘s chest or back of the neck, and connects to the nose using a custom nasal cannula with completely separate lines for left and right nostrils. Airflow in the nose generates a pressure wave through the cannula that is registered at the sensors. The processor then converts pressure back to air flow, that can be stored on the device or transmitted via Bluetooth. The device was tested and approved for safety by the Israeli Ministry of Health.

The device is used in two contexts: 1. Ongoing nasal respiration for 24 hours, with special attention to the nasal cycle, i.e., the left/right asymmetry in nasal airflow that is indicative of autonomic tone [49], and 2. The "sniff-response", i.e., an automatic modulation in nasal airflow in accordance with odorant properties [50]. Both the 24-hour recording and odor experiments are initiated via a cellphone-based application.

For the 24-hour nasal airflow recording, the nasal cycle is assessed by the Laterality Index (LI). This index measures the flow ratio between the left and right nostrils, calculated using: $$\textrm{LI}=\frac{\left({\textrm{Flow}}_R-{\textrm{Flow}}_L\right)}{\left({\textrm{Flow}}_R+{\textrm{Flow}}_L\right)}$$ for every minute. The result of this calculation is a one-minute resolution time series of lateralization extent, with a value of 1 representing airflow through the right nostril only, a value of -1 representing airflow through the left nostril only, and a value of 0 representing equal flow across nostrils [49]. Healthy adults have a nasal-cycle shift every ~2 hours during wake, and ~4.5 hours in sleep. Frequency of shifting is expected to diminish as a function of severity of DoC. Slightly reduced shifting in MCS, and no, or near-no shifting in UWS are hypothesized.

In the odor experiment, at each trial, jars containing a pleasant odorant, unpleasant odorant, or blank stimulus are presented to the patient. An audible voice instructs the patient to "please prepare to sniff the odor at the tone, three, two, one” followed by a 1-second beep-tone. The experimenter brings the jar to under the patient‘s nose at the "beep" count, and removes it after five seconds. This procedure is repeated 30 times (10 times for each odor stimulus, random order), with ~30s ISI, resulting in a total experiment duration of ~15 minutes. Using this data, we test for a sniff-response, namely a modulation in nasal airflow in accordance with the odorant. A sniff-response is defined as a trial meeting at least one of the the two following criteria: 1) an odorant-induced reduction in sniff magnitude of 15% or more in relation to baseline respiration. 2) a air-flow standad deviation across all trials in the session of more than 0.35. Meeting either of these criteria implies MCS rather than UWS [50]. These two hypotheses, namely a nasal-cycle and sniff-response reflecting levels of consciousness, may enable the addition of a simple tool to the arsenal of instruments used in assesement of DoC.

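### The sniff-response is defined for a trial, but one of its two criteria belongs to the whole session and the other has no rule leading from 20 odorant trials to the patient

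*Protocol article*

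**What the plan says.** The odor experiment is described in the protocol article under Measures and data analyses, Nasal airflow and respiration.

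- **Stimuli:** "jars containing a pleasant odorant, unpleasant odorant, or blank stimulus are presented to the patient".
- **Trials:** "This procedure is repeated 30 times (10 times for each odor stimulus, random order". With two odorants and one blank, this gives 20 odorant and 10 blank trials.
- **Unit of the definition:** "A sniff-response is defined as a trial meeting at least one of the the two following criteria".
- **Criterion 1:** "an odorant-induced reduction in sniff magnitude of 15% or more in relation to baseline respiration".
- **Criterion 2:** "a air-flow standad deviation across all trials in the session of more than 0.35".
- **Consequence:** "Meeting either of these criteria implies MCS rather than UWS".
- **Status of the marker:** "These two hypotheses, namely a nasal-cycle and sniff-response reflecting levels of consciousness" are what the experiment is meant to examine.

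The section gives no minimum number or share of positive trials, no averaging for criterion 1 and no contrast between odorant and blank trials. It also gives no breath-to-breath variability, no error rate for the call, and no unit for the 0.35 threshold.

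**The concern.** The definition mixes two units. Criterion 2 describes a session, so it cannot sort one trial from another. Taken at its word, once it is met all 30 trials become sniff-responses, blanks included. Criterion 1 can be applied to a trial, but the article then moves straight to the patient's state with nothing in between. If one trial is enough, each patient has 20 opportunities to be positive by chance.

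The comparator for criterion 1 adds to this. The spoken countdown, the tone and the approaching jar accompany every trial. Comparison with baseline respiration alone cannot separate their effect from that of the odor. The blank trials could, but they have no stated role in criterion 1. They do enter criterion 2, whose standard deviation covers all trials.

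At stake is the marker's ability to separate MCS from UWS, and consistency across sites: two teams could score the same recording differently and both claim to follow the text. The section on multilayer integration compares how well each modality's markers classify, so a badly scored sniff variable would distort its own evaluation.

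**Working it through.** The article states no error rate for this marker, so there is no figure to reproduce. Its own counts agree: 3 stimuli × 10 = 30 trials, and 30 × about 30 s = about 15 minutes.

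**Inputs from the article:** 20 odorant trials, 10 blank trials, a 15% threshold for criterion 1 and 0.35 for criterion 2.

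**Assumptions, not in the article:** no odor effect; sniff magnitude divided by baseline is normal with mean 1 and standard deviation s; baseline known without error; trials independent unless stated.

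**Step 1. Literal reading: any one of 20 odorant trials suffices.** Per trial, p = Φ(−0.15/s). For the session, P = 1 − (1 − p)^20.

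| s | p | P(at least one of 20) |
|---|---|---|
| 0.05 | Φ(−3.00) = 0.0013 | 2.7% |
| 0.10 | Φ(−1.50) = 0.0668 | 75% |
| 0.15 | Φ(−1.00) = 0.1587 | 97% |
| 0.20 | Φ(−0.75) = 0.2266 | 99.4% |

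Without assuming normality, p can be varied directly: p = 0.001 gives 2.0%, 0.01 gives 18%, 0.05 gives 64% and 0.10 gives 88%. A session rate of 90% needs p = 1 − 0.10^(1/20) = 0.109, and 95% needs 1 − 0.05^(1/20) = 0.139.

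**Step 2. Correlated trials.** With a common correlation r between trials, P is 1 minus the average over a standard normal u of [1 − Φ((−0.15/s − √r·u)/√(1 − r))]^20.

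| s | r = 0 | r = 0.3 | r = 0.5 |
|---|---|---|---|
| 0.10 | 75% | 53% | 41% |
| 0.15 | 97% | 79% | 65% |
| 0.20 | 99.4% | 88% | 76% |

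With complete dependence, P falls to p.

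**Step 3. Session-level reading: criterion 1 on a mean.** For one mean of n independent trials the chance rate is q = Φ(−0.15·√n/s). For the pooled odorants n = 20. If either of two per-odorant means may count, n = 10 and the rate is 1 − (1 − q)².

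| s | Pooled mean of 20 | Either of two means of 10 |
|---|---|---|
| 0.20 | 0.04% | 1.8% |
| 0.30 | 1.3% | 11.1% |

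Correlation works the other way here. The standard deviation of the pooled mean becomes s·√((1 + 19r)/20). At s = 0.20 and r = 0.3 this is 0.20 × √0.335 = 0.116, and the chance rate is Φ(−0.15/0.116) = 9.8%. A disturbance common to all trials, such as an error in the baseline, also shows in the blanks. That is the reason to compare with them.

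**Step 4. Criterion 2.** If 0.35 is on the same normalised scale, which the article does not say, the chance that the standard deviation of 30 trials exceeds it is P(χ²₂₉ > 29 × (0.35/s)²). This is below 0.1% at s = 0.20 and 9.3% at s = 0.30. Since either criterion suffices, this adds to the rate from criterion 1.

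**The case against.** The strongest reply is that the article nowhere says in words that one positive trial is enough. Criterion 2 can only be met by a session, so the sentence drawing the conclusion about MCS reads most coherently at session level for both criteria, and the reference to a trial is a drafting slip. On that reading the 20-fold multiplicity disappears. This stands as a reason to make the rates in Step 1 conditional. It does not rescue the text: if the session is intended, the stated unit is wrong and the statistic for criterion 1 is still unstated.

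A reader might infer that almost every UWS patient would be labelled MCS, or that specificity is close to zero. The documents do not support that. It requires that one trial suffices and that p is about 0.11 to 0.14 or more with independent trials, and none of this is given. The 0.35 threshold cannot be used to pin down s, because its unit is not given and it pools odorant and blank trials.

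It can also be said that criterion 1 requires the drop to be caused by the odorant, which excludes an effect of the voice or the jar. The wording does ask for that, but the only comparator stated is baseline respiration, which cannot show it.

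Finally, the marker is a hypothesis under test and feeds a multimodal classifier assessed by cross-validation and across sites. Nothing says that a positive call becomes the patient's diagnosis. Table 1 provides for results to be communicated to caregivers, but no text says that this call is reported to them. This limits the harm downstream. The article may leave scoring detail to a fuller document, but here it does state a definition, thresholds and a consequence, and these do not fit together.

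**Conclusion.** The point holds as a defect in a stated rule. The unit error follows from the text alone and needs no assumption: criterion 2 cannot be a property of a trial. Criterion 1 has no rule from 20 odorant trials to the patient and no stated contrast with the blanks.

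The size is conditional. If one odorant trial suffices, the chance of a false indication of MCS from criterion 1 is 2.7%, 75%, 97% and over 99% at s = 0.05, 0.10, 0.15 and 0.20, with no odor effect and independent normal trials. Correlation between trials lowers these figures; at r = 0.5 they are still 41% and 65% at s = 0.10 and 0.15. If the session is meant, the multiplicity goes and the remaining fault is an undefined statistic. Either way the definition has to be corrected before the marker is scored and compared with the others.

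**What to change.** 1. Remove the reference to a trial from the definition and state both criteria for the session.
2. Apply criterion 1 to the mean baseline-normalised sniff magnitude over the odorant trials, keeping the 15% threshold. Compute the same mean on the 10 blank trials as the within-patient control, and say how the two are compared.
3. State whether the odorants are pooled. If either per-odorant mean may count, give the two-test chance rate: about 11% at s = 0.30, against 1.3% for the pooled mean, with independent trials.
4. Keep criterion 2 as an explicit session-level standard deviation and give the unit or normalisation of 0.35.
5. Replace the statement that meeting a criterion implies MCS with the estimated sensitivity and specificity of the session-level call, since the section itself presents the marker as a hypothesis. Observed trial-to-trial variability and correlation should be reported with them, because the chance rates depend on both.

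The cost is a change of wording and re-scoring of airflow already recorded, with no new acquisition. Fewer patients will be sniff-positive, and pooling pleasant with unpleasant odorants may blur a response specific to one of them.
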